### Primary outcome measure

#### Physical performance

The short physical performance battery (SPPB) [63] will be used to evaluate lower extremity physical performance status. The SPPB has been adopted in various studies, especially in those of aging [63–66], and has shown to be associated with mobility disability, future institutionalization and mortality [64, 67, 68]. The test battery comprises three objective timed tests: 1) gait speed test, 2) five chair-stands test, 3) balance test. The gait speed test measures the time needed for walking a distance of four meter at normal pace. The chair-stands test measures the time needed to complete five sit to stands as quickly as possible without using upper extremity assistance. In the balance test, the participants are advised to hold their balance in three standing positions with eyes open: feet side-by-side position, feet in a semi-tandem position and feet in tandem stand. Each stance will be demonstrated to the participant by the study investigator before participant attempts. A score from 0 (being unable to complete the task) to 4 (highest level of performance) will be assigned to each performance. By summing the three individual scores, a total physical performance score will be created, with higher scores indicating better lower body function [63]. As these tasks mimic daily activities, this is an important outcome measure for patients with GvHD. The instrument has been used successfully in a collective of hemato-oncological patients [69] and in previous trials investigating physical performance in cancer patients [70–72].

### Secondary outcome measures

#### Muscle strength

A hand-held dynamometer (device from CITEC©, Netherlands), which is a recommended instrument to measure muscular strength in cancer patients [73], will be applied to assess maximal voluntary isometric muscle contraction in Newton meters in six muscle groups (knee and elbow flexors and extensors, hip flexors and abductors). Results of a study by Knols et al. [74] indicate that there is acceptable reliability for evaluating muscle strength with a hand-held dynamometer in patients with hematological malignancies. Strength test will be conducted in standardized test positions according to Bohannon [75]. The patient will be instructed to perform maximum contraction during dynamometry measures. Muscle groups will be assessed bilaterally for their isometric power. The maximum force applied within 3 s of effort will be recorded. For each muscle group, measurement will be carried out in triplicate. The best value will be used in the analysis. In addition, a hand-grip strength test will be performed using a digital hand dynamometer RFM (DHD-1) of the brand saehan. Measurement will be taken from both hands in a sitting position with the elbow extended and arm parallel to, but not touching, the side of the body. After the demonstration of the technique, the investigator will instruct the patient to perform maximum contraction during the measures. For each hand, the patient will perform three valid sets. The maximum value (in kg) within 3 s of effort will be recorded. Both procedures are well-established and have been used in hematological cancer populations [33, 35, 38, 76, 77].

#### Submaximal endurance capacity

The 6 min walk test will be used to determine the submaximal endurance capacity [78]. The test will be performed according to the American Thoracic Society protocol [79]. Briefly, patients will be instructed to walk as fast as possible on a flat, easy-to-walk track for 6 min. The total distance walked in 6 min under maximal effort conditions will be measured. Further, heart rate and O_2_-saturation will be assessed before, during and after the test and the individual perceived exhaustion will be measured using the Borg-Scale [80]. The 6 min walk test has been reported to have good psychometric properties in a variety of areas including cancer patients [81]. It is a simple and safe test which has previously been used in allo HSCT patients [35, 38, 76]. The formula by Enright et al. [82] will be used for reference.

#### Muscle volume

Ultrasound measurement will be performed to determine the thickness and cross-sectional area of both vastus lateralis muscles as well as subcutaneous adipose tissue thickness. Muscle ultrasound measurement is a non-invasive and safe measurement. Both in elderly people and in younger populations, studies showed a good reliability of muscle ultrasound and a good validity compared with MRI, CT or DEXA yet [83, 84]. Reliability and validity of our standardized ultrasound examination protocol to quantify vastus lateralis muscle was shown in a recently conducted study [85].

Patients will be sited in supine position with a soft roll below the hollow of their knees. They will be instructed to relax their leg muscles during the whole examination. The distance between the upper patella pol and the spina iliaca anterior superior will be measured and three measurements sites will be marked on the skin in the middle, the lower and upper third of the vastus lateralis muscle (VL) using a flexible tape measure. On each measurements site, the medial and lateral edges of VL belly will be identified by ultrasound. Then again, a flexible tape-measure will be used to connect the medial and lateral edge of VL by drawing a line and to mark the mid-point of this distance. This point will be defined the reference point for each measurements site. On each reference point, three fixed images of VL will be taken. For measuring muscle cross sectional area, the extended field of view software (LOGIQview, GE Healthcare GmbH) will be used reconstructing panoramic images of VL belly.

#### Quality of life

Patients’ quality of life will be assessed using the validated 30-item self-assessment questionnaire of the European Organisation for Research and Treatment of Cancer (EORTC QLQ-C30, version 3.0). It is composed of five functional multi-item scales (physical, role, emotional, cognitive, and social function), three symptom multi-item scales (fatigue, pain, nausea/vomiting), one global health status multi-item scale, and six single items for remaining symptoms [86]. The EORTC QLQ-C30 will be supplemented by the EORTC QLQ-HDC 29 module. This 29-item questionnaire assesses the quality of life during and after high-dose chemotherapy and stem cell transplantation [87]. It consists of 6 multi-item scales and 8 single-item questions. Scoring will be performed in accordance with the EORTC scoring manual [88].

#### Fatigue

The score of the EORTC QLQ-FA 12 will be used to assess physical, emotional and cognitive fatigue in participants. The EORTC QLQ-FA 12 is a self-assessment questionnaire of the European Organisation for Research and Treatment of Cancer and an internationally validated phase IV module. It is composed of 12 questions, 10 unidirectional and 2 criteria variables which measure the extent to which fatigue interferes with daily activities and social life [89]. Scores will be derived according to the EORTC scoring manual.

#### GvHD symptom burden

The original Lee chronic GvHD Symptom scale has been recommended for use in clinical practice and trials by the 2005, 2014 and the 2020 National Institutes of Health Consensus Conference [90–92]. In this study, the modified 7-day Lee Chronic-versus-Host Disease Symptom Scale (mLSS) will be used to capture the GvHD-specific symptom burden. The mLSS is a 28 item, 7-domain symptom scale (skin, eyes, mouth, lung, nutrition, energy and psych) that takes 2 min to complete. Patients will report their level of symptom bother over a period of 7 days on a 5-point Likert scale. Scoring will be performed according to the scoring algorithm. The mLSS is a reliable and valid instrument for evaluating GvHD symptoms [93]. According to authors of the mLSS, a 5 to 6 change in the summary score suggests a clinically meaningful difference in patient’s symptomatology [93].

#### Nutritional status

Nutritional status will be screened and adopted regulatory and performed individualized with multiple tools. First, the Nutritional Risk Screening (NRS 2002), a validated screening tool for detecting malnutrition in hospitalized settings, is used [94]. NRS includes a pre-screening, containing four yes/no-questions about body mass index, weight loss, food intake and disease severity. By answering at least one question with yes, the main screening will be performed, specifying and ranking the questions from pre-screening and also considering patients age. A total score > 3 implements a risk for malnutrition and requires further nutritional adjustment. Scores < 3 require regular repetition.

Based on NRS an individual nutritional counselling according to nutritional guidelines of the German Society for Nutritional Medicine and the European Society for Clinical Nutrition and Metabolism is performed. Weekly counseling includes monitoring of relevant blood parameters (e.g. serum albumin and total protein) and ensuring the daily calorie (25-30 kcal/kg bodyweight/d) and protein needs (1.2–1.5 g protein/kg body weight/d) are fulfilled. Finally, hand grip strength (see section muscle strength), known as a marker of muscle function and good nutritional state is performed regularly [95, 96].

#### Performance status

The Karnofsky performance scale will be applied to assess functional status of a patient. The Karnofsky performance scale is a 11-point rating scale, which ranges from normal functioning (100%) to dead (0%) [97]. The scale is widely used due to its psychometric properties and recommended in clinical assessments [91, 98].

### Study sample

Patients are considered eligible for study participation if they meet the following inclusion criteria:Present acute or chronic GvHD which is currently treated with systemic steroidsAge ≥ 18 yearsSufficient mastery of the German language in order to understand and follow the study protocolWilling/able to train twice a week live-online supervised by sport therapists, or at exercise facilities at the National Center for Tumor Diseases or at certified training facilitiesWilling to take part in the scheduled assessmentsAbility to consent and give written informed consent

Exclusion criteria are:Any physical or mental condition that would hamper the performance or interfere with the exercise program or the completion of the study procedures, e.g.Heart insufficiency > NYHA III or uncertain arrhythmiaUncontrolled hypertensionSevere renal dysfunction (GFR < 30%, Creatinine> 3 mg/dl)Reduced standing or walking abilityInsufficient hematological capacity (either hemoglobin value below 8 g/dl or thrombocytes below 30.000/μL)Any other comorbidities that preclude participation in the exercise programs

### Sample size

To our knowledge no supervised, progressive moderate-to-high intensity resistance exercise study in a GvHD population treated with systemic steroids with the primary endpoint physical performance measured via the SPPB exists, as of yet. Consequently, the effect size for the primary outcome measure is unknown. The sample size calculation for the present exploratory project is based on a conservative estimation, using a mean standardized effect size of 0.5. To detect a corresponding effect with ANCOVA at a significance level of 5% with a power of 80%, 42 participants per group are required. Based on unpublished data of a previous study of ours, we expect a drop-out rate of 15% and a mortality rate of 10%. Consequently, 56 subjects per group need to be enrolled.

### Recruitment and randomization

The goal is to recruit 112 patients within an inclusion period of 2.5 years. Recruitment will take place at the University Hospital in Heidelberg - Section stem cell transplantation. All potentially eligible patients seen by their treating hematologist will be invited to participate in the study and will be referred to the case management. The case manager will provide eligible patients with the study flyer and the patient information. Further, they will obtain patients’ consent to be contacted by the study investigators via phone. On a daily basis, study investigators will collect the consent forms of referred patients and contact them by phone to provide further information on the study, review interest and eligibility. In case interested patients contact study investigators directly, they will be informed about the main aspects of the study and initially screened for eligibility. Patients who are still interested in participating in the study after the initial phone contact are invited to have an in-person discussion. During that discussion, participants have the opportunity to ask remaining questions about the research and express concerns. Before written informed consent will be obtained, the study investigators seek verbal assurance that the patient understands the study aim, its interventions and procedures and that the participation is entirely voluntary. Study investigators will inform the patient that his/her approval may be withdrawn at any time, for any reason, and without disadvantages for further medical care. Patients who are still willing to participate then need to provide written informed consent. No financial incentives for subjects who take part in the research study are offered. Upon written informed consent, an appointment for baseline assessment will be scheduled. Patients who are not willing to participate are asked to provide the reasons for non-participation.

After the completion of the baseline measurements, patients will be randomly assigned to one of the two arms with a 1:1 allocation, using REDCap (Research Electronic Data Capture) randomization module (automated assignment system) [99, 100]. To avoid imbalance between the arms, block randomization procedure is applied. Stratification factors for the randomization include intensity of conditioning for allo HSCT (reduced-intensity vs myeloablative), haploidentical transplantation (yes vs. no) and type of GvHD (acute vs. chronic). The allocation table has been generated with R [101] by an project-independent employee of the research department based on the given requirements.

Allocation concealment will be ensured, as the randomization module will not release the code until the patient has been recruited into the trial and has completed the baseline assessment. After assignment to one of the arms, neither participants nor staff can be blinded to allocation due to the nature of interventions and staffs’ direct involvement within the intervention program (e.g. training organization, phone calls about participants’ wellbeing).

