### Data collection and management

Participants will be required to attend the University Hospital Heidelberg on five occasions. All study visits will be planned, if possible, with routine care visits. All assessments will last between 1.5–2 h. Participants will be advised to wear comfortable shoes and clothes and to arrive hydrated to the study visit. Assessments will be done by study investigators, who have been extensively trained. Moreover, a number of pilot tests were performed prior to the study. To maintain high methodological quality, internal inspections of the methods will be carried out. Data will be collected and managed using REDCap electronic data capture tools hosted at the University Hospital Heidelberg. REDCap is a secure web application for building and managing databases developed at Vanderbilt University and launched in 2004 [99, 100]. Data will be entered digitally throughout each assessment using a mobile tablet. Only study investigators will have access to the REDCap project and will be able to do entries. The principal investigator and the study coordinator will have the right to unlock entries after assessment completion to do major adjustments. To assure high data quality, background validation has been installed for the majority of variables. Remaining variables will be checked for logic by study coordinator.

When participant attends the assessment, he/she will be asked to complete a survey using a mobile tablet. The survey includes sociodemographic questions, questions on fatigue, GvHD symptoms and on quality of life. Patients will receive immediate feedback when implausible values have been given, hence, responds can be adjusted. If assistance is needed, the study investigators will administer participants via interview. In case of tablet rejection, participant can respond on a paper-based questionnaire. After completion, physical assessments will be conducted, followed by the nutritional assessment. Patients will be contacted via telephone for the following assessment appointments.

Reasons for drop-out throughout the study will be recorded where possible. No further data will be collected in patients who withdrew from the study.

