### Exercise intervention

Participants of the experimental group receive, in addition to nutritional endorsement, a supervised progressive moderate-to-high-intensity resistance training program. Depending on their medical condition and Covid-19 precautions and immune status patients have the opportunity to train live-online or at our exercise facility at the National Center for Tumor Diseases (NCT) or at certified training facilities near their home provided by the network OnkoAktiv.

Participants will be provided with an exercise intervention booklet. The booklet, written in plain language, contains educational information about physical exercise and cancer, information about the exercise intervention process, weekly physical activity logs and a catalogue with illustrated exercises (~ 15) for strengthening the muscles. Moreover, patients will receive stretch bands with different levels of tension. After the handover, the booklet will be discussed verbally with the participant by the study investigators, to ensure comprehension.

Regardless of the training location, participants will be supervised by an experienced exercise therapist or physiotherapist. Introductory training sessions will be scheduled before the start of the intervention program in order to screen the patients and to adapt the program in case of physical limitations. Each training session begins with a low-intensity warm-up (5–10 min stretching or mobility exercises), followed by the resistance training regime (45 min), and a cool-down (5–10 min) which will include stretching of major muscle groups. Online exercise session will be offered in small groups on weekday afternoons in order to ensure that participants who have medical appointments or other commitments are able to participate.

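### The reasons given for leaving all staff unblinded do not explain why the SPPB assessor or the ultrasound measurer must know the arm

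*Protocol article*

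**What the plan says.** Under Recruitment and randomization, the protocol article says that after assignment "neither participants nor staff can be blinded to allocation due to the nature of interventions". The same sentence gives a second reason, the staff's "direct involvement within the intervention program (e.g. training organization, phone calls about" how participants are doing).

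The tasks are divided as follows.

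- **Assessment.** Data collection and management says: "Assessments will be done by study investigators, who have been extensively trained".
- **Database.** The same section says: "Only study investigators will have access to the REDCap project and will be able to do entries". The randomization module runs in REDCap too.
- **Session supervision.** Exercise intervention says that, wherever training takes place, "participants will be supervised by an experienced exercise therapist or physiotherapist".
- **Booklet.** Exercise intervention also says that "the booklet will be discussed verbally with the participant by the study investigators, to ensure comprehension".
- **Primary outcome.** Physical performance says: "The test battery comprises three objective timed tests". One of these is five chair stands done at maximum speed.
- **Ultrasound.** Muscle volume says: "On each reference point, three fixed images of VL will be taken". Panoramic views are then reconstructed for cross-sectional area. No reader is named. Table 1 schedules ultrasound at t0, t3 and t4.

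The Discussion lists the unblinded investigators and participants as a limitation.

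**The concern.** The article treats blinding as one question for everybody. There are at least three groups: patients, people who deliver the training, and people who measure outcomes. An exercise intervention cannot be hidden from the first two. Nothing in its nature reveals the arm to someone holding a stopwatch or tracing a muscle outline, unless that person also delivers it or can look up the allocation.

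Baseline is completed before the allocation is released, so it is measured without knowledge of the arm, while t1–t4 are measured with it. The primary analysis is an ANCOVA of SPPB change to the end of the intervention. An assessor effect that differs by arm therefore enters the t3 value only and passes directly into the treatment estimate. Randomization does not protect against this.

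The chair stands, dynamometry and the 6-minute walk all respond to how the patient is instructed and encouraged. A small positive result would be harder to attribute to the training.

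**Working it through.** **1. Test each stated reason against each role.**

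| Role | Nature of the interventions | Staff involvement in the programme |
|---|---|---|
| Patient | explains it | not applicable |
| Session supervisor | explains it | explains it |
| SPPB, walk and strength assessor | does not explain it | only because of how tasks are divided |
| Measurer of ultrasound images | does not explain it | only because of how tasks are divided |

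For the last two rows the article gives an organisational reason, not an impossibility.

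**2. How far the roles overlap now.** Session supervision is given to therapists. Study investigators assess, go through the exercise booklet with participants, and have REDCap access. Training organisation and calls are attributed to staff, without saying which staff. Masking an assessor therefore needs a deliberate rule covering booklet handover, organisation, calls and REDCap view.

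**3. Reproduce the planned sample size, which the illustration uses.** Sample size gives d = 0.5, 80% power and 42 per group by ANCOVA; the statistical section gives two-sided 5%.

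- No covariate: n = 2 × ((1.96 + 0.8416)/0.5)² = 62.8, so 63 per group.
- ANCOVA with baseline correlation r: n = 62.8 × (1 − r²). Setting n = 42 gives r² = 1 − 42/62.8 = 0.331, so r ≈ 0.575. With r = 0.58, n = 42 and power is 80.3% by the normal approximation. The noncentral t needs r ≈ 0.59 for 80%.
- Losses: 15% + 10% = 25%; 42/0.75 = 56 per group, 112 in total, as planned.

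Masking the assessor alters none of these figures.

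**4. Hypothetical illustration of an assessor bias.** The documents give no SPPB SD, no bias and no correlation. Assume:

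- SD = 1.5 to 2.5 points, so that d = 0.5 equals 0.75 to 1.25 points;
- bias: one experimental patient in five gains one point, i.e. 0.2 × 1 = 0.2 points, which is 0.2/1.25 = 16% to 0.2/0.75 = 27% of the target effect;
- no true effect, 42 per arm.

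SE in SD units = √(1 − r²) × √(2/42). For r = 0.59 this is 0.807 × 0.218 = 0.176. The noncentrality is (bias/SD)/SE; for SD 1.5 it is 0.133/0.176 = 0.757. Two-sided rejection probabilities from the noncentral t:

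| Assumed bias | r | SD 1.5 | SD 2.0 | SD 2.5 |
|---|---|---|---|---|
| 0.2 points | 0.59 | 11.6% | 8.7% | 7.3% |
| 0.2 points | 0 | 9.3% | 7.4% | 6.5% |
| 0.1 points | 0.59 | 6.6% | 5.9% | 5.6% |
| 0.1 points | 0 | 6.0% | 5.6% | 5.4% |

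The result moves with every assumed input. It shows that a modest one-sided bias would matter at this sample size, not that such a bias will occur.

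**The case against.** The strongest reply is that the trial is candid and not careless. It calls itself exploratory and discloses the missing blinding. It describes trained assessors, pilot tests, internal inspection of methods, standardised strength positions, a published walk-test protocol and an ultrasound procedure with tested reliability. The SPPB is timed and each task is scored 0 to 4, so a nudge must carry a patient across a category boundary. Only the chair stands ask for maximum speed; gait is at usual pace and balance means holding set positions. Patients with reduced standing or walking ability are excluded, which may limit room for upward drift.

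Most of this stands and limits the size of the problem. None of it hides the arm from the assessor, and disclosure does not reduce bias.

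A reader might infer more than the documents support, in four ways:

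- **That delivery and assessment are already largely separate.** Only session supervision is clearly assigned to others. The stated staff involvement and the booklet discussion show overlap.
- **That stored ultrasound images are ready for blind reading.** The article says images are taken; it does not mention archiving or say whether measurement is live or offline. Coding would mask measurement only, since site marking and edge finding happen during scanning.
- **That full assessor masking needs no extra people.** Team size is not given. A dedicated additional assessor may not be affordable, so full separation can be asked for only where the team allows.
- **That 7–12% is an expected error rate.** It rests wholly on assumed values.

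**Conclusion.** The point holds in a limited form. The two stated reasons do not show that the SPPB assessor or the ultrasound measurer has to know the arm. The first does not apply to them and the second is a choice about tasks. The resulting detection bias is partly avoidable, most clearly in the measurement of ultrasound images, and the article contains no step aimed at it.

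Its size is unknown. The false-positive range is conditional on assumed SD, bias and correlation, and the conclusion does not depend on it. Masked assessment would reduce the assessor's part of the bias; unblinded patients' own effort would still differ by arm, so a small positive result would be easier to interpret but not free of doubt. This is an improvement that should be made, not a flaw that invalidates the trial.

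**What to change.** Within the existing staff:

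1. **Ultrasound.** Save vastus lateralis images under a code that shows neither arm nor visit, and measure them in batches. State that this masks measurement, not acquisition.
2. **Script.** Use one fixed instruction and encouragement script for SPPB, 6-minute walk and dynamometry in both arms.
3. **Assessor.** Where the team allows, have t1–t4 assessments done by an investigator who has not handed over the booklet, organised sessions or made calls for that patient. Hide the allocation field in that person's REDCap view and record any unmasking. Where this is not possible, say why.
4. **Wording.** In Recruitment and randomization, state that patients and trainers are unblinded and that assessors are masked where possible. Bring the limitation in the Discussion into line.

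The cost is coded image files, a short script, a user-rights setting and a constraint on scheduling visits that already take 1.5–2 hours and are combined with routine care where possible. Patients will sometimes reveal their arm. Enrolment stays at 56 per group, 112 in total.
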